### Staff training and awareness

Study-specific training is provided for staff at all participating hospitals by the study co-ordinating centre team based at Newcastle University.

### Sample size

The sample size calculation is based on the premise that clinician-assigned more likely diagnosis currently does not separate the study population into groups with significantly different risks of stroke. As it is currently unknown whether the 90 day risk of stroke following a likely diagnosis of TIA with migrainous symptoms is the same as typical TIA (ie, 10%) and how this might be affected by prevention treatments, to power this study the TIA with migrainous symptoms event rate has been conservatively set much lower at 1%. The day 90 risk of stroke in the migraine group has been set at 0.015% based upon the previously reported average incidence of stroke in true migraine sufferers 58/100 000 patients/year.^22^,^24^ At 90% power and a two-sided significance level of p=0.05, a total of 2574 participants (1287 per group) are required to detect this difference (or a greater difference) in stroke rate between specialist assigned more likely diagnosis of migraine and TIA with migrainous symptoms groups. Inflating for a 5% loss in case of routine data access difficulties or allocation of an ‘unclear’ independent adjudication label for any observed outcome events results in an overall target of 2709 participants.

A cohort of this size is also sufficient to examine whether stroke can be predicted by multiple explanatory variables. If the stroke rate in the TIA with migrainous symptoms group is the same as previous TIA cohorts (10%), then at least 128 outcome events are expected.

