**Trial registration number:**

ISRCTN16775533.

STRENGTHS AND LIMITATIONS OF THIS STUDYStudy A in this project is a large observational cohort study sufficiently powered to determine the risk of stroke for people with migrainous symptoms reviewed as suspected TIA.The inclusion of study B, a qualitative co-design process to inform the visualisation of a risk assessment tool and barriers/facilitators to implementation, will support future adoption into clinical services.A limitation of this project is that external validation of the risk prediction model is not planned due to available resources; only internal validation will be undertaken.

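### The 90% power depends on a 0.015% stroke rate from people with true migraine, applied to a clinician-labelled possible-migraine group in which some missed TIA is expected

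*Protocol article*

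**What the plan says.** The Sample size section of the protocol article starts from the premise that "clinician-assigned more likely diagnosis currently does not separate the study population into groups with significantly different risks of stroke". It then fixes two 90-day stroke rates.

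- **TIA with migrainous symptoms:** a typical TIA risk is given as 10%, but "the TIA with migrainous symptoms event rate has been conservatively set much lower at 1" per cent.
- **Migraine:** "The day 90 risk of stroke in the migraine group has been set at 0.015" per cent, based on the "previously reported average incidence of stroke in true migraine sufferers 58/100 000 patients/year".

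For 90% power and a two-sided 5% test, the result is stated as follows: "a total of 2574 participants (1287 per group) are required to detect this difference (or a greater difference"). A 5% allowance for loss brings the target to 2709.

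Other sections describe who will be in the migraine group. Under Population, patients are at least 40 years old, are reviewed as suspected TIA, and carry a symptom-based diagnosis of possible migraine or possible TIA. The Background says that the two conditions are hard to tell apart and that diagnosis may vary with the assessor's specialty and training. The Discussion says that no definition of migraine is imposed.

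The strengths and limitations box describes Study A as "sufficiently powered to determine the risk of stroke" in this population.

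**The concern.** The 0.015% describes people who truly have migraine. The group in the comparison is made up of people whom a clinician thinks more likely to have migraine, after a referral for suspected TIA. Using the first rate for the second group assumes almost no missed TIA, yet possible missed TIA is a reason for doing the study.

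The direction of the error is known. With the TIA rate fixed, a lower migraine rate widens the assumed difference and reduces the required sample. The 1% was set cautiously; the 0.015% works the other way.

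The stated 90% power could therefore be well above the power actually available. A non-significant comparison would then say little about whether diagnosis separates risk. The article's claim about determining risk is a separate matter, because the calculation sizes a difference between groups and not the precision of a risk estimate.

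**Working it through.** **Inputs from the Sample size section.** p1 = 0.01 (TIA group), p2 = 0.00015 (migraine group), two-sided alpha 0.05 (z = 1.960), power 90% (z = 1.282), equal groups.

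**1. Source rate.** 58/100,000 × 90/365 = 0.0143%, or 0.0145% if the annual rate is divided by 4. Both are consistent with the rounded 0.015%.

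**2. The plan's sample size.** With mean rate p = (p1 + p2)/2 = 0.005075 and d = p1 − p2 = 0.00985:

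n' = [1.960 √(2p(1−p)) + 1.282 √(p1(1−p1) + p2(1−p2))]² / d² = 1091.6, so 1092 without correction.

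Continuity correction: n = (n'/4) × [1 + √(1 + 4/(n'd))]². Here n'd = 10.75, so n = 272.9 × (1 + √1.372)² = 1286.6, rounded up to 1287.

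The stated figure reproduces. 2574/0.95 = 2709.5, which agrees with 2709 to within rounding.

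**3. What the rates imply.** Expected strokes are 1287 × 0.01 = 12.9 in the TIA group and 1287 × 0.00015 = 0.19 in the migraine group. The chance of no stroke in the migraine group is (1 − 0.00015)^1287 = 0.82. A single stroke there would be 1/1287 = 0.078%, about five times the assumed rate. The assumed risk ratio is 0.01/0.00015 = 67.

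**4. Power at 1287 per group, TIA rate held at 1%.** The first power column inverts the continuity-corrected formula of step 2. The second enumerates all outcomes under two binomials and applies Fisher's test. Migraine rates other than 0.015% are assumptions.

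| Migraine rate | Plan's formula | Exact Fisher |
|---|---|---|
| 0.015% | 90% | 98% |
| 0.1% | 81% | 88% |
| 0.2% | 66% | 71% |
| 0.3% | 50% | 53% |
| 0.5% | 24% | 24% |

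**5. Mislabelling, with the TIA rate varied too.** Suppose 20% of the migraine group carries the TIA-group risk (an assumption). Its rate is then 0.2 × p1 + 0.8 × 0.015%.

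| TIA rate | Migraine-group rate | Exact power |
|---|---|---|
| 1% | 0.212% | 69% |
| 2% | 0.412% | 96% |
| 3% | 0.612% | 99.7% |

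At a TIA rate of 2% with a migraine rate of 0.5%, exact power is 93%.

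**6. What a null result would show.** If both groups had the same rate p, the 95% half-width for the difference would be 1.96 × √(2p(1−p)/1287). This is 0.54 percentage points at p = 0.5% and 0.77 at p = 1%, so the interval is about as wide as the risks themselves.

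**7. Precision of the overall risk.** The planned rates give 12.9 + 0.19, about 13 strokes in 2574. That is 0.51%, with an exact 95% interval of 0.27% to 0.86%.

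**The case against.** Several points on the other side are sound.

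- **A reader might infer that the section contradicts itself**, by presuming no separation and then powering for a 67-fold ratio. The premise reads naturally as the null hypothesis and the two rates as the alternative. Any calculation for detecting a difference has that form, so there is no contradiction. What remains open is the value chosen for the alternative.
- **A reader might infer that the plan calls both rates conservative.** It applies that word only to the 1%.
- **A reader might infer that 0.015% is the most favourable rate available.** The document gives no competing rate for this group, so that cannot be said.
- **A reader might infer that p > 0.05 will be taken as equal risk.** The article does not say so. Nor does the risk model depend on the comparison: it is built irrespective of the assigned diagnosis.
- **The low 1% gives real protection.** It is a tenth of the typical TIA risk quoted, and step 5 shows that a TIA rate of 2% or 3% absorbs much of the optimism in the migraine rate. Even at 1%, a migraine rate of 0.1%, nearly seven times the assumed value, leaves 88% exact power.
- **Interval methods and power tables may be in documents not shown**, and group proportions are already to be reported.

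These points narrow the concern but do not remove it. The rate, its source and the 90% are all printed in the article, and nothing there explains why a true-migraine incidence suits a clinician-labelled group.

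**Conclusion.** The concern holds in a limited form. The sample size arithmetic is correct, but the 90% is conditional on a migraine-group rate that leaves almost no room for mislabelled TIA, in a study that expects some.

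At the planned 1% TIA rate, power drops to 66% by the plan's formula (71% exact) if the migraine-group rate is 0.2%, and to 24% by either method at 0.5%. These rates, and the 20% mislabelling, are illustrative; the documents give no figure for either. The loss is serious only if the TIA rate is close to 1% and the migraine rate is about 0.2% or more.

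Two smaller points stand beside it. A non-significant result could not show that diagnosis fails to separate risk, given the interval widths in step 6. The claim that the study is powered to determine risk does not follow from a calculation that sizes a difference. This should be fixed, but it does not undermine the design.

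**What to change.** 1. In Sample size, justify the migraine rate for a group defined by clinician opinion. Failing that, state that the 90% is conditional on 0.015%, and add a small table of power over a joint range of both rates, such as migraine rates of 0.015% to 0.5% against TIA rates of 1% to 3%.
2. In Statistical analysis, report the risk in each group and the risk difference with exact or score 95% intervals. State that a non-significant result will not be taken as showing that diagnosis does not separate risk.
3. In the strengths and limitations box, replace the statement about power to determine risk with the expected precision: at the planned rates about 13/2574 = 0.51%, exact 95% interval 0.27% to 0.86%.

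The cost is wording and one table. No extra patients are needed. The stated power will look less favourable over part of the range. The article reports 586 participants enrolled in November 2025, with follow-up due to finish in February 2027, so the change can be made before the outcomes are analysed.

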## Background

 Stroke affects 110 000 UK citizens each year at a health and social care cost exceeding £9 billion.^1 2^ National healthcare policy aims to reduce stroke-related disability and its wider impact through targeted primary and secondary prevention.^3^ Before a stroke, many patients experience a Transient Ischaemic Attack (TIA), which is a brief episode of neurological impairment due to a temporary reduction in cerebral blood flow. TIA is associated with a 5% risk of stroke after 7 days and 10% during the next 90 days.^4 5^

Although medical treatments cannot completely eradicate stroke risk, meaningful reductions can be achieved.^6 7^ For example, antiplatelet medication produces an absolute risk decrease between 1.1% to 3.6% according to the agent(s) and population.^8^ Therefore, it is important to promptly and accurately identify TIA so that personalised prevention can be initiated and patients given relevant information, such as temporary restrictions on driving. In the NHS, there is a target for patients with suspected TIA to be reviewed by a specialist hospital service within 24 hours of symptoms being reported to initiate appropriate early treatment including antiplatelet, lipid lowering and/or blood pressure control medication, anticoagulation for atrial fibrillation, and surgical endarterectomy if carotid stenosis is present.^6 9 10^

The incidence of first-ever TIA is approximately 50 per 100 000 people per year;^4 5^ however, there are approximately twice this number of referrals to TIA services because of diagnostic uncertainty.^11^ While many TIAs produce classic movement, sensory, speech and visual impairments lasting <20 minutes on a background of vascular risk factors such as hypertension and diabetes, other conditions can cause transient neurological symptoms. Typically half of the referrals made to TIA services are given a different possible or definite diagnosis following specialist review.^11^

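### The cohort is declared sufficient for the stroke prediction model on a 10% event rate, but it is sized on 1%, at which about 13 strokes are expected

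*Protocol article*

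**What the plan says.** Two paragraphs of the Sample size section (protocol article, Study A) matter here.

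- The first explains that "it is currently unknown whether the 90 day risk of stroke following a likely diagnosis of TIA with migrainous symptoms is the same as typical" transient ischaemic attack, and that for this reason "the TIA with migrainous symptoms event rate has been conservatively set much lower at 1" per cent. For the other group, "The day 90 risk of stroke in the migraine group has been set at 0.015" per cent. The design settings come next ("At 90% power and a two-sided significance level of p=0.05"), and the result is that "a total of 2574 participants (1287 per group) are required to detect this difference". A 5% allowance for losses brings the target to 2709.
- The second turns to the prediction model: "A cohort of this size is also sufficient to examine whether stroke can be predicted by multiple explanatory variables". The supporting sentence is conditional: it applies if the rate among those given the TIA diagnosis "is the same as previous TIA cohorts (10%), then at least 128 outcome events are expected".

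No event count is given at the 1% rate. The section on prognostic model and risk assessment tool development then describes multiple regression on demographics, symptoms and previous medical history, with backward stepwise selection and bootstrap internal validation. The outcome is any stroke by 90 days in the whole cohort.

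**The concern.** The section treats 10% as too uncertain to power the group comparison and falls back on 1%. It then uses 10% as the only ground for calling the cohort large enough for the model. The two rates differ tenfold, and the information available to a model for a rare binary outcome is governed mainly by the number of events.

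The condition sits on the event count, not on the sufficiency statement. A reader would take it that the model is adequately supported by design, when at the section's own planning rate the expected number of strokes is about a tenth of the figure shown. The model and its risk tool are objective 6 and part of the project aim in the Abstract. An overstated basis for them carries over into how the tool's predictions are received and into the options shown to clinicians in the final round of Study B.

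**Working it through.** **Inputs (all from Sample size).** TIA-with-migrainous-symptoms rate 1% for power and 10% for the model; migraine rate 0.015%; two-sided 0.05; 90% power; 1287 evaluable per group, 2574 in total.

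**1. Which rate sizes the cohort.** The two-proportion formula with p1 = 0.01, p2 = 0.00015 and mean 0.005075 is

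n = [1.960 x sqrt(2 x 0.005075 x 0.994925) + 1.282 x sqrt(0.01 x 0.99 + 0.00015 x 0.99985)]^2 / 0.00985^2 = 1092 per group after rounding up.

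With the continuity correction, (n/4) x [1 + sqrt(1 + 4/(n x 0.00985))]^2 = 1287 per group. The stated size reproduces exactly, so 1% is the rate on which the cohort is built.

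**2. The stated event count.** 1287 x 0.10 = 128.7. The 128 reproduces at 10%, counting the TIA group only.

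**3. The same count at other rates** (adding 1287 x 0.00015 = 0.19 in the migraine group):

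| TIA-group rate | TIA group | Total |
|---|---|---|
| 1% (planning rate) | 12.87 | 13.1 |
| 5% (illustrative) | 64.35 | 64.5 |
| 10% | 128.7 | 128.9 |

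The Poisson 95% range around 13.1 is about 7 to 21. Half of the full 2709 with no losses gives 1354.5 x 1% = 13.5 in the TIA group, so the allowance for losses does not change the picture.

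**4. Sensitivity to the group split.** An observational cohort does not enforce 1:1. For an assumed TIA share of 30% to 70% of 2574, still at 1% and 0.015%:

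- 30%: 7.72 + 0.27 = 8.0 strokes
- 70%: 18.02 + 0.12 = 18.1 strokes

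**5. What such counts support.** The number of parameters for expected shrinkage S is p = n x (S - 1) x ln(1 - R2cs/S), with n = 2574 and S = 0.9. R2cs is an assumed Nagelkerke R2 of 0.15 or 0.30 multiplied by the maximum Cox-Snell R2 at that event fraction. Neither the R2 values nor S come from the documents.

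| Events | Maximum R2cs | p at R2 0.15 | p at R2 0.30 |
|---|---|---|---|
| 13 | 0.061 | 2.7 | 5.3 |
| 64 | 0.208 | 9.1 | 18.5 |
| 129 | 0.328 | 14.5 | 29.8 |

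Rounded down, that is 2 to 5, 9 to 18 and 14 to 29 parameters.

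**6. Against the planned predictors.** Counting only the domains that the modelling section names, Table 1 lists 5 demographic items, 21 symptom items and 9 medical history items: 35 in all, before sides, subtypes and repeat episodes. That is 13.1/35 = 0.4 events per item at the planning rate and 128.9/35 = 3.7 at 10%.

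**The case against.** The strongest reply is that the 128 is openly conditional and correctly multiplied, and that the section already admits the true rate is unknown. That stands, and it rules out some stronger readings:

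- **That the 128 is a miscalculation.** It is not. It follows from 1287 and 10%.
- **That its lower-bound wording is false.** Within the stated condition it is defensible: the figure is rounded down and leaves out migraine-group strokes, which can only add. It is not a floor over all the rates the section considers, but the sentence does not claim that.
- **That the protocol's own text shows 10% cannot apply.** The Background says "TIA is associated with a 5% risk of stroke after 7 days and 10% during the next 90 days", and entry is allowed up to a week after the last symptoms. It is tempting to conclude that half the risk has passed by entry. But nesting the first figure inside the second is a reading, one week is a maximum delay, the Background also gives a 24-hour review target, and no delay distribution is reported. Nor is any figure given for the effect of excluding previous stroke or planned surgery.
- **That no multivariable model could be fitted.** Step 5 still allows 2 to 5 parameters at 13 events.
- **That a limit on predictors is missing.** That is normal analysis-plan content, and the plan is not shown.

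The protocol also has safeguards: bootstrap validation, simple as well as complex tool options, and a statement in Study B of what remains useful if predictive performance is unsatisfactory. These reduce the harm. They can reveal optimism after the event, but they do not supply events or correct the statement that the size is sufficient.

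**Conclusion.** The point holds as an unsupported sufficiency claim, not as an arithmetic error. The protocol asserts without condition that the cohort is large enough for multivariable prediction, and the design does not have that property at its own planning rate. About 13 strokes are expected there, roughly a tenth of the count offered in support, and they would carry only a very small model. At 10% the claim is reasonable for a model of moderate size; the fault is that it is not confined to that case.

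The figure of 13 rests on the stated 1% and 0.015% rates and an even split, with about 8 to 18 over the assumed range of splits. The parameter counts also rest on the assumed R2 values and the shrinkage target. The true rate is unknown and may lie well above 1%. The conclusion concerns what the document can claim in advance, not a forecast that the model will fail.

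**What to change.** Replace the last two sentences of the Sample size section with text that:

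1. Gives expected strokes among 2574 evaluable participants as about 13 at 1%, about 64 at 5% and about 129 at 10%, assuming equal groups.
2. Makes sufficiency for multivariable prediction conditional on the higher rates.
3. States that the number of candidate parameters will be set from the observed pooled stroke count, before any predictor-outcome analysis, with the criterion named (for example, expected shrinkage of at least 0.9).
4. States that near 13 events only a minimal penalised model is supportable, alongside the absolute-risk estimates already planned under objective 2.

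The cost is wording, carried through to the analysis plan. The stated ambition for the model becomes less favourable. No extra patients or data are needed, and with 586 enrolled in November 2025 and follow-up due to finish in February 2027, the change can be made before the model is built.

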### Statistical analysis

#### Cohort description and stroke risk

Data will be presented for the total cohort, specialist clinician more likely diagnosis of migraine group and specialist clinician more likely diagnosis of TIA with migrainous symptoms group. This will include:

Summary descriptive statistics for baseline characteristics, investigations and treatments.Proportions suffering first hospitalisation for stroke by 90 days.Number and timing of stroke events by 90 days (in case of multiple events).Clinical characteristics of stroke events (including clinical and radiological subtype; symptom severity; emergency treatments received).

The proportion of patients experiencing any stroke, defined as at least one clinically documented stroke hospital admission during the next 90 days, will be compared between the specialist clinician more likely diagnosis of migraine group versus the TIA with migrainous symptoms group.

Specialist diagnosis, treatments and 90 day stroke rate across all study patients will also be reported according to:

The professional background of the clinician performing the assessment.The mode of assessment (in person vs remote).Other important service characteristics (eg, referral volume).

Exploratory analyses may also consider:

The clinician confidence rating for their diagnosis (very high/high/uncertain) for migraine or TIA with migrainous symptoms.Patients with single versus multiple stroke events.

#### Prognostic model and risk assessment tool development

Development of the risk assessment tool will combine information from both Study A and Study B. Using the stages described by Moons *et al*^25 26^ and applying Transparent Reporting of a Multivariable Prediction Model for Individual Prognosis or Diagnosis (TRIPOD) Statement principles,^27^ a prognostic model will be developed through multiple regression to examine the association between clinical characteristics recorded during initial specialist TIA review (including demographics, symptoms and previous medical history) and the 90 day occurrence of any stroke. The initial model will contain all baseline factors independently associated with day 90 stroke and those nominated as plausible by clinicians during Study B initial co-design rounds. Backward stepwise regression will retain variables for the final prognostic model. The performance of the model will be summarised using calibration and discrimination measures. To correct for overfitting and optimism in model performance, an internal validation using bootstrap samples will be performed which splits the data into training and test samples multiple times.

Approaches to visually represent the prognostic model (eg, nomogram)^28^ will be prepared and shared with clinicians during the final round of the study B co-design process to confirm clinical sense and meaning. These will include simple and more complex risk tool options and their matching predictive performance statistics. Options will include clinician preferences about risk assessment tool format identified during the earlier co-design rounds. The final tool preferred by clinicians is expected to reflect a balance between predictive performance and a format/content which is suitable for real world clinical use^29^ e.g. it can be completed within the time restrictions of clinical care with information that is often available, while retaining acceptable utility.

